#### Laboratory tests

The purpose of laboratory tests in this study is to evaluate the safety and pharmacokinetic profiles of SRS and OB. Because of the small number of patients assigned to this study and the different baseline values for each individual patient, we will not perform a detailed statistical analysis. However, if significant abnormal results are found in the laboratory tests, the clinical laboratory results will be described, and the connection to the drug will be considered.

Blood tests will be conducted at 0, 2, 4 and 8 weeks, and urine tests will be performed at 0 and 4 weeks during the clinical trial. In the case of a participant who drops out or the early termination of the clinical trial, blood and urine tests will be performed on the last day of the trial.

Using the test results (comprehensive verification of vital signs, laboratory tests, ECGs and physical examinations) for each individual patient, the investigator will determine adverse reactions caused by the drugs, and statistical tests will be conducted as needed on clinically significant parameters.

#### Test of human derivatives

IBS is known to be closely related to stress.^12^ Therefore, we plan to quantify factors associated with stress or that have been reported to worsen IBS symptoms as follows: (1) cortisol, (2) corticotropin-releasing hormone, (3) serotonin, (4) group I cytokines (10 species), (5) group II cytokines (14 species) and (6) growth factors (3 species).^33 34^ Serum will be separated from blood specimens collected at 0, 4, 8 weeks, stored frozen and transferred to the Korea Institute of Oriental Medicine for examination.

#### Early termination or dropout

The criteria for early termination or dropout are as follows: (1) administration of other drugs that are expected to affect the safety and efficacy of the clinical trial drugs; (2) request of participants to discontinue the clinical trial or withdrawal of the trial agreement; (3) occurrence of significant adverse drug reactions or events that preclude continuing the trial, according to the judgement of the clinical investigator; (4) new discovery of violations of significant clinical trial protocol during clinical trial; (5) less than 70% trial drug compliance and (6) any other reason that the clinical trial should be discontinued at the discretion of the clinical trial manager or investigator.

#### Data collection, access and management

The data of this trial will be managed according to the standard work instructions of Catholic Kwandong University International, St. Mary’s Hospital. Other contents not specified in the trial protocol shall follow the standards of the International Council for Harmonisation of Technical Requirements for Pharmaceuticals for Human Use (ICH) guideline for Good Clinical Practice and Korean Good Clinical Practice guideline.

The source document is recorded immediately when the data are collected. After the source document input is completed, it will be recorded in the case report form (CRF). All the documents will be kept safe, so that the data can be verified by the relevant government agencies and the IRB. Only research colleagues and others who have been approved by the principal investigator will have access to all data obtained from this trial.

#### Statistical analysis

The statistical analysis will be conducted by blinded professional statisticians. To evaluate the efficacy of the study, both an intent-to-treat (ITT) analysis (primary analytical method) and a per-protocol (PP) analysis (secondary analytical method) will be performed. The ITT analysis will be conducted for all patients who were followed up at least once after randomisation and will be able to be evaluated for effectiveness. The PP analysis will be performed for patients who complete the 8-week treatment course and meet the inclusion and exclusion criteria.

To analyse the continuous variables in the demographic information and pretreatment characteristics between groups, a one-way analysis of variance (ANOVA) and Kruskal-Wallis test will be conducted. An ANOVA and Kruskal-Wallis test will also be used to test for symptom improvement compared with baseline (0 week) and the variables for analysis that include the following: (1) subjective symptom improvement (primary outcomes) and (2) severity of symptoms related to D-IBS (abdominal pain, abdominal discomfort, satisfaction of defecation, frequency of abdominal pain and quality of life). All values will be shown as mean±SEM. Comparisons of outcome assessments between the four groups will be performed using the paired t-test or Wilcoxon signed-rank test.

If the Subject’s Global Assessment of Relief on the Likert scale is ‘0’ or ‘1’ for more than 2 weeks between weeks 8 and 12, then the symptoms will be considered to have improved sufficiently. Based on this, we will calculate the symptom relief rate by dividing the number of participants who exhibited sufficient symptom relief by the total number of participants in the trial and present descriptive statistics. The CATMOD procedure will be used to evaluate the improvement of symptoms compared with baseline. Comparisons between the four groups will be conducted using the χ^2^ test or Fisher’s exact test. These statistical analyses will also be performed at 2, 4, 6, 8 and 10 weeks from baseline. The Cochran-Mantel-Haenszel test will be used to confirm the difference between the intervention groups at each time point.

A statistical analysis will also be conducted to evaluate safety. The incidence of adverse events and abnormality of experimental results will be analysed statistically according to the groups, and non-parametric methods will be applied as necessary using a paired t-test for continuous data, McNemar’s test for categorical data, Fisher’s exact test for adverse events and a generalised estimating equation for clinically significant changes between groups.

All statistical analyses will be conducted using SAS software, V.9.1.3 (SAS institute). A P value <0.05 will be considered statistically significant.

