### Rescue therapy and concomitant medications

Participants are prohibited from taking any medication that could affect D-IBS during the entire course of the trial. However, if serious side effects occur or symptoms worsen, investigators will provide quick and appropriate treatment (including drug administration), based on their medical judgement. In this case, the direct investigators will record the treatment or drug administration and report to the IRB within 24 hours to determine whether the trial should be continued or discontinued.

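### The primary set labelled ITT is a modified ITT set with an undefined evaluability condition and a mismatched relief-rate denominator, and late relief scores may be lost in relation to outcome

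*Protocol article*

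**What the plan says.** All references are to the protocol article.

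- **Role of the sets** (Statistical analysis): "both an intent-to-treat (ITT) analysis (primary analytical method) and a per-protocol (PP) analysis (secondary analytical method) will be performed".
- **Primary set** (same section): "The ITT analysis will be conducted for all patients who were followed up at least once after randomisation", and who "will be able to be evaluated for effectiveness". The article does not say at which time point, or for which endpoint, a patient must be evaluable.
- **Per-protocol set** (same section): "The PP analysis will be performed for patients who complete the 8-week treatment course and meet the inclusion and exclusion criteria".
- **Relief rate** (same section): a patient has sufficient relief if the relief score is 0 or 1 for more than 2 weeks between weeks 8 and 12. The number of such patients is divided by the number of all trial participants, not by the ITT set.
- **Tests of the 0–4 score** (same section): ANOVA and Kruskal-Wallis.
- **Leaving the trial** (Early termination or dropout): the criteria include "administration of other drugs that are expected to affect the safety and efficacy of the clinical trial drugs" and "less than 70% trial drug compliance".
- **Treatment of worsening** (Rescue therapy and concomitant medications): investigators may treat worsening symptoms, including with drugs, and then "report to the IRB within 24 hours to determine whether the trial should be continued or discontinued".
- **Assessment at dropout** (Laboratory tests): "In the case of a participant who drops out or the early termination of the clinical trial, blood and urine tests will be performed". No efficacy assessment at or after dropout is described anywhere in the article.
- **Timing** (Design; Primary outcome): the relief question is asked at weeks 2, 4, 6, 8 and 12, with weeks 2 and 6 by telephone.

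**The concern.** An intention-to-treat set is fixed at randomisation. This one depends on two later events: being followed up, and being evaluable.

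The second condition is the more troublesome because it is open to interpretation. The relief criterion uses weeks 8 to 12, so an analyst could decide that a patient who leaves at week 4 is not evaluable for it. On that reading the primary set for the responder endpoint would demand later data than the per-protocol set, which requires only the 8-week course. The text neither states nor rules out that reading.

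The dropout criteria add a second route to loss. Poor compliance and use of other drugs can follow from lack of relief or from side effects. The Hypothesis section expects efficacy to differ between arms, so these losses may differ between arms too. If scoring stops at that point, the late 0–4 scores that enter the ANOVA and Kruskal-Wallis tests come from a group selected partly by outcome. With about 20 patients per arm, a few such losses can move a comparison.

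**Working it through.** **1. The plan's own figure.** The Sample size calculation section gives 16 completers per arm and 20% expected dropout. 16 / (1 − 0.20) = 20 per arm, and 4 × 20 = 80. The stated 20 and 80 reproduce. The expected number of dropouts is 80 × 0.20 = 16, leaving 64 completers.

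**2. How many patients the follow-up condition excludes.** The first efficacy contact is at week 2, so only patients lost before then fail this condition. The article does not give the timing of dropout, so it is assumed here.

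| Share of the 16 dropouts lost before week 2 | Size of the set |
|---|---|
| 0% | 80 |
| 25% | 80 − 4 = 76 |
| 50% | 80 − 8 = 72 |
| 75% | 80 − 12 = 68 |
| 100% | 80 − 16 = 64 |

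Under a constant dropout rate with 20% lost by week T, the fraction lost before week 2 is 1 − 0.8^(2/T):

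- T = 8: 1 − 0.8^(0.25) = 0.0543, so 80 × 0.0543 = 4.3 lost and a set of about 76.
- T = 12: 1 − 0.8^(1/6) = 0.0365, so 80 × 0.0365 = 2.9 lost and a set of about 77.

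On the follow-up condition alone, about 3 to 4 of 80 are excluded, and the set is nearer to all randomised patients than to completers.

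**3. How many late scores could be missing.** If scoring stops at dropout, up to 16 of 80 patients (4 of 20 per arm) have no score by the end of treatment (T = 8) or of follow-up (T = 12). They remain in the set if they passed week 2, but they have no late value for the ANOVA or Kruskal-Wallis test unless a missing-data rule supplies one.

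**4. What the denominator does to the relief rate.** As an illustration, assume 8 of 20 patients respond in each arm and all those lost are non-responders.

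| Lost, arm A / arm B | Rate on observed patients | Rate on all randomised |
|---|---|---|
| 4 / 4 | 8/16 = 50% in both | 8/20 = 40% in both |
| 2 / 6 | 8/18 = 44.4% versus 8/14 = 57.1%, gap 12.7 points | 8/20 = 40% in both, gap 0 |

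The choice of denominator decides whether a false difference can arise in this example. The article states the safe one in substance, but it does not match the ITT set defined in the same section and is not given per arm.

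**The case against.** A reader might infer that the primary analysis is close to a completer analysis, or that the relief rate will be about 10 points too high. The document supports neither.

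- A patient removed after the week 2 contact has already met the follow-up condition. Completers form a separate set, the per-protocol set. The primary set falls to 64 only if every expected dropout leaves before week 2, or if evaluable is taken to mean evaluable in weeks 8 to 12, which the text does not say.
- The relief rate is divided by all participants. On the illustrative figures that gives 8/20, not 8/16, and the inflation disappears. The 50% and the 12.7-point gap would arise only with an observed-case denominator, and they also assume that every lost patient is a non-responder.
- It would also be too strong to say that late scores of dropouts are never collected. The sentence naming blood and urine tests stands in the laboratory section, where one would not expect efficacy assessments. The Design section has the coordinator encouraging follow-up at every visit, and after treatment for worsening symptoms continuation is decided case by case.
- Handling of missing values may be set out in the full protocol or SAP, neither of which is shown, so its absence from the article is no fault.

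All of this stands, and it limits the point to its narrower form. It does not remove three things that the article itself states: a set called ITT that depends on events after randomisation, an undefined evaluability condition, and a denominator that belongs to a different population. Nor does it protect the comparisons of the 0–4 score, to which the relief-rate denominator does not apply.

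**Conclusion.** The point holds in a limited form. The primary set is a modified ITT set under the wrong name, its evaluability condition can be read in materially different ways, and it does not agree with the relief-rate denominator. Because compliance below 70% and use of other drugs count as early termination or dropout, and no later efficacy assessment is described, late 0–4 scores may be missing for reasons linked to efficacy or tolerability.

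The ANOVA and Kruskal-Wallis comparisons of those scores are exposed. The relief rate is not exposed in this way if its denominator is all randomised patients.

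The size of any bias is unknown. The figures of about 3 to 4 of 80 excluded from the set, and up to 16 of 80 without late scores, rest on the planned 20% dropout. The first also assumes a constant dropout rate, and the second assumes that scoring stops at dropout. Nothing in the article says how much of the 20% would come from the two criteria quoted.

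**What to change.** 1. Define the primary set as all randomised patients, analysed in the arm to which they were allocated. Keep the present set if wanted, call it modified ITT, and state what evaluable means.
2. Use all patients randomised to each arm as the denominator of that arm's relief rate. A patient without an observed response in the week 8 to 12 window then counts as a non-responder, which fits the existing responder definition.
3. Separate stopping study drug from leaving the study for purposes of data collection. Leave the clinical stopping criteria unchanged, and keep asking the relief question at the contacts already scheduled unless consent is withdrawn.

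The cost is some rewording and a few extra contacts with patients who have stopped study drug. Reported response rates would be slightly lower wherever an observed-case denominator would otherwise have been used. The trial status section describes recruitment as ongoing, so the third change could still benefit patients not yet through follow-up at that time.

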**Methods and analysis:**

This trial is a randomised, double-blinded, placebo-controlled, double-dummy, four-arm, parallel study. After a 2-week preparation period, 80 patients with D-IBS will be randomly assigned to one of four treatment groups consisting of SRS (water extract granules, 5 g/pack, three times a day) with OB (tablet form, one capsule three times a day) or their placebos, with treatment lasting for 8 weeks. Post-treatment follow-up will be conducted 4 weeks after the end of treatment. The primary outcome is the finding obtained using the Subject’s Global Assessment of Relief method. The secondary outcomes are the severity of symptoms related to D-IBS, determined using a 10-point scale, and the change in symptoms.

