### Design

This study is a placebo-controlled, double-blind trial. Eighty patients will be enrolled and randomly assigned to four separate arms of the trial. The trial will be conducted at Catholic Kwandong University International St. Mary’s Hospital, Incheon, South Korea.

The study subjects will be required to participate in a 2-week preparation period (weeks −2 to 0) and an 8-week drug-administration period (weeks 0–8). The patients will visit four times, on weeks 0, 4, 8 and 12. The primary outcome measurement will be evaluated at weeks 2, 4, 6, 8 and 12, and the secondary outcome measurement will be evaluated at weeks 0, 2, 4, 6, 8 and 12. Participants will be assessed for efficacy and safety of the treatment through visits (0, 4, 8 and 12 weeks) and telephone questionnaires (2 and 6 weeks). In addition, laboratory tests will be conducted at 0, 4 and 8 weeks. According to the intervention protocols, the clinical research coordinator (CRC) will encourage patients and participants to complete follow-up at every visit.

During the drug-administration period, SRS or its placebo will be given as one pack of water extract granules three times a day, 30 min before each meal. OB or its placebo will be given as one tablet three times a day, 30 min before each meal.

Participants will be divided into four groups: (1) SRS and OB group, (2) SRS and placebo-OB group, (3) placebo-SRS and OB group and (4) placebo-SRS and placebo-OB group. The entire flow chart of the study is shown in figure 1.

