
### Recruitment, randomisation, blinding and non-blinding

Advertisements for the study will be posted at the Catholic Kwandong University International St. Mary’s Hospital using banner advertisements and posters. We also plan to post the advertisements on the hospital home page, in the monthly hospital magazine, at the internet café and on the subway at least five times. All these advertisements will be done with the approval of the IRB.

After recruitment, patients will be randomised to one of the four trial arms. Randomisation will be performed using a list of block randomisations made by statisticians, independent of this clinical trial. A researcher who is not involved in the process of drug prescription and evaluation will execute the randomisation process.

During the treatment period, the patients and all researchers (investigators and CRCs) will be blinded, except the researchers who conducted the randomisation procedure. In addition, the researchers will not know the kind of medication that is being administered to the patient or any other information that could lead to bias.

Allocation concealment will be performed during the process of medication administration. The management pharmacist, who will not be involved in analysing the results of the trial, will use the randomisation table to label the medication with the assignment number and provide the medication. The patients will take the drugs contained in the opaque envelope, which will be labelled with the assignment number.

Non-blinding will be performed only in the following situations: (1) if the trial is terminated and there is a need for statistical analysis; (2) if a serious medical emergency occurs and information about the medication is needed and (3) if the chief investigator determines that non-blinding is necessary.

The entire process of the study will be directed by the authorised clinical research organisation (CRO), DreamCIS, Seoul, Korea.

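### Paired tests are assigned to between-arm comparisons of the score outcomes in a parallel trial; independent-group tests should be named instead

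*Protocol article*

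**What the plan says.** The Abstract gives the design: "This trial is a randomised, double-blinded, placebo-controlled, double-dummy, four-arm, parallel study". The Design section adds: "Eighty patients will be enrolled and randomly assigned to four separate arms of the trial". The section on recruitment and randomisation says: "After recruitment, patients will be randomised to one of the four trial arms". None of these describes matching or crossover.

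The Statistical analysis section then makes four statements about efficacy tests:

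- On improvement: "An ANOVA and Kruskal-Wallis test will also be used to test for symptom improvement compared with baseline (0 week"), applied to the relief score and the symptom severity scales.
- On the arms: "Comparisons of outcome assessments between the four groups will be performed using the paired t-test or Wilcoxon signed-rank test".
- On the symptom relief rate, a responder measure built from the relief score: "Comparisons between the four groups will be conducted using the χ^2^ test or Fisher’s exact test".
- On the separate weeks: "The Cochran-Mantel-Haenszel test will be used to confirm the difference between the intervention groups at each time point".

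For safety, the same section says that "non-parametric methods will be applied as necessary using a paired t-test for continuous data". It also lists McNemar's test for categorical data, Fisher's exact test for adverse events and a generalised estimating equation for changes between groups.

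**The concern.** The paired t-test and the Wilcoxon signed-rank test are one-sample tests on within-pair differences. Patients in different arms are independent and form no pairs, and neither test handles four groups at once. The sentence that says how outcome assessments are compared between arms therefore names tests that cannot do it.

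Hypothesis 1 compares the combination with each single drug, and hypothesis 2 compares each active arm with placebo. Both are contrasts between two arms. For the score outcomes, no valid two-arm test is named. An analyst who follows the text must either invent a pairing or fall back on a before-after test in each arm. The second course credits natural improvement and placebo response to treatment.

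**Working it through.** **The plan's own figure.** The Sample size calculation section takes 16 completers per arm and 20% dropout: 16 / (1 − 0.20) = 20 per arm, and 4 × 20 = 80. This reproduces. No effect size, SD or power is given, so the improvement sizes below are assumptions, shown as a range.

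**Reading 1: the paired test is run across arms.**

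- *Row order.* One data set of 20 per arm was simulated with a true difference of 0.8 SD. The independent two-sample t-test gave p = 0.012. Over 5,000 re-orderings of one arm, the paired p-value ran from 0.00004 to 0.061.
- *Degrees of freedom.* With 20 per arm they fall from 2 × 20 − 2 = 38 to 20 − 1 = 19.
- *Unequal arms.* Assume 20 per arm, each patient completing independently with probability 0.80. The chance of equal completer counts is the sum over k of P(k)² for two arms and of P(k)⁴ for four, with P binomial(20, 0.80). This gives 0.158 and 0.0055, or about 16% and 0.5%. Otherwise some patients have no partner.
- *Error rate.* With arbitrary random pairing and no true difference, the simulated false-positive rate was 4.6% to 5.2%. The type I error is not inflated.

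**Reading 2: the paired test is run before-after within each arm.**

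- *Relief score.* The Design and Primary outcome sections collect it at weeks 2, 4, 6, 8 and 12. There is no week 0 value, so a before-after pair does not exist.
- *Severity scales.* Assume normal change scores with SD 1, identical arms with the same mean improvement d, and a two-sided 0.05 level; 20,000 trials were simulated per setting. Let p be the chance that one arm's own test is significant. Arms are independent, so the chance that the combination is significant and placebo is not is p(1 − p).

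| Per arm | d (SD) | p | p(1 − p) | Simulated |
|---|---|---|---|---|
| 16 | 0.3 | 0.206 | 0.164 | 0.166 |
| 16 | 0.5 | 0.466 | 0.249 | 0.250 |
| 16 | 0.8 | 0.844 | 0.132 | 0.128 |
| 16 | 1.0 | 0.961 | 0.037 | 0.035 |
| 20 | 0.3 | 0.250 | 0.188 | 0.187 |
| 20 | 0.5 | 0.565 | 0.246 | 0.241 |
| 20 | 0.8 | 0.924 | 0.070 | 0.073 |
| 20 | 1.0 | 0.988 | 0.012 | 0.010 |

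With no improvement in any arm (d = 0), the simulated figure was 4.6% (16 per arm) or 4.4% (20 per arm).

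**Comparator.** In the same simulations, the two-sample t-test and one-way ANOVA on change were falsely significant, in either direction, in 4.6% to 5.3% of trials at every d.

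**The case against.** The best defence is that valid between-arm tests stand close by. The χ² or Fisher's exact test is named for the relief rate, which derives from the primary outcome, and the Cochran-Mantel-Haenszel test for differences at each time point. ANOVA and Kruskal-Wallis are named for improvement in both kinds of score and, run across arms, give a valid overall test. Independent-group tests are attached to change from baseline and paired tests to group comparison, so the roles look swapped. This stands, and it narrows the point. A reader might infer that hypotheses 1 and 2 rest wholly on paired tests; the document does not support that. What remains is that, for the scores, the sentence on group comparison names the wrong tests, and an overall test does not supply the two-arm contrasts that the hypotheses need.

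A reader might also infer that the between-arm results would be invalid in the sense of too many false positives. Arbitrary random pairing keeps the error near 5%. The defect there is an order-dependent answer that wastes information.

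The before-after figures depend on judging arms by which of them reaches significance, and the protocol states no such rule. It is also tempting to say that two identical arms would disagree on significance in half of trials. The formula 2p(1 − p) does give 49–50% at 0.5 SD, but that is near its maximum of 50%. At 1.0 SD it is about 7% (16 per arm) or 2% (20 per arm).

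Finally, a reader might say that the safety paragraph repeats the error. Its paired t-test and McNemar's test can be read as within-arm tests, beside Fisher's exact test and a generalised estimating equation for group differences. The Laboratory tests section also says that those data will get no detailed statistical analysis. Only a wording note is warranted there.

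**Conclusion.** The point holds for the 0–4 relief score and the 0–10 severity scales: as written, the between-group sentence names tests that cannot compare independent arms. It does not reach the relief rate, and it does not show that the trial lacks a valid between-arm analysis.

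If severity scores were judged arm by arm, the false pattern of combination significant and placebo not would occur in about 13–25% of trials with 16 per arm, or 7–24% with 20, against about 5% for a two-sample test. This assumes identical arms, normal change scores and a common improvement of 0.3 to 0.8 SD. With no improvement, or with 1.0 SD, the figure is below 5%. It does not apply to the relief score, which has no week 0 value. That the two families of tests were swapped is likely but cannot be confirmed from the document.

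**What to change.** Replace the between-group sentence so that score outcomes are compared between arms with independent-group tests:

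- overall: ANOVA or Kruskal-Wallis;
- for the arm pairs in hypotheses 1 and 2: two-sample t-test or Wilcoxon rank-sum test;
- for the severity scales, where a week 0 score is available: baseline-adjusted ANCOVA.

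Keep the paired t-test and the signed-rank test for within-arm description only. In the safety paragraph, state that the paired t-test and McNemar's test are within-arm, and correct the wording that presents the paired t-test as a non-parametric method.

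The cost is rewording, and the sample size of 80 does not change. One check is needed before ANCOVA is named: the Design section lists week 0 for the secondary outcomes, but the Secondary outcomes section starts the severity scales at week 2. If no week 0 severity score is collected, the unadjusted two-sample tests still apply to the follow-up scores.

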### Outcome measurements

#### Primary outcome

The primary outcome will be measured via a questionnaire that confirms subjective symptom improvement. Participants will respond a total of five times during and after the administration period (at 2 and 6 weeks via telephone, and at 4, 8 and 12 weeks during direct visits) to the following question: Subject’s Global Assessment of Relief—‘How much do you think the symptoms of D-IBS have improved compared to before the clinical trial?’ According to the answers given by the patients to this survey, the improvement is given a score of 0, 1, 2, 3 or 4.

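### The symptom-relief rule does not fit the relief schedule: patients whose week 8 and week 12 scores differ or are missing cannot be classified, and the week-10 analysis has no data

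*Protocol article*

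**What the plan says.** Statistical analysis section: a Subject's Global Assessment of Relief of 0 or 1 "for more than 2 weeks between weeks 8 and 12, then the symptoms will be considered to have improved sufficiently". The number of patients meeting this rule is the numerator of a symptom relief rate. The rate is to be presented descriptively, and the same paragraph goes on to CATMOD, χ² or Fisher's exact, and Cochran-Mantel-Haenszel analyses. On timing it adds: "These statistical analyses will also be performed at 2, 4, 6, 8 and 10 weeks from baseline".

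Design section: "The primary outcome measurement will be evaluated at weeks 2, 4, 6, 8 and 12". The drug is given in weeks 0 to 8, and the Abstract places one follow-up contact 4 weeks after treatment ends.

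Primary outcome section: "Participants will respond a total of five times during and after the administration period", by telephone at weeks 2 and 6 and at visits in weeks 4, 8 and 12. The single question asks for improvement relative to the time before the trial. It asks nothing about how long any improvement has lasted.

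**The concern.** The rule sets a minimum duration of relief inside a four-week window, but the plan collects a score only at the two ends of that window. The quantity that the rule needs is not observed. The analysis list also names a time point at which no relief score exists.

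Someone will therefore have to decide what the rule means in practice: both scores qualifying, either one, the last one, or something else for patients without a week 12 score. If that decision is made after the treatment codes are known, it is a post hoc choice of endpoint. With about 20 patients per arm, moving a few patients between responder and non-responder can change the comparison.

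**Working it through.** **The plan's own figure.** The document gives no relief rate, effect size or power, so there is no stated rate to reproduce. The one relevant figure is the sample size: 16 completers per arm with 20% dropout gives 16 / (1 − 0.20) = 20 per arm, and 4 × 20 = 80. This reproduces and is not affected. It is used below only to turn shares into counts.

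**Step 1: set the schedule against the rule.** Relief scores: {2, 4, 6, 8, 12} (Design; Primary outcome). Window: weeks 8 to 12 (Statistical analysis).

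- Scores in the window, ends included: {8, 12}, two scores.
- Scores strictly inside it: none.
- Scores up to the end of treatment: {2, 4, 6, 8}. Scores after treatment: {12}.
- Planned repeat analyses {2, 4, 6, 8, 10} against the schedule: weeks 2, 4, 6 and 8 match. Week 10 has no score. Week 12 has a score but is not listed.

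A rule tied to weeks 8 to 12 cannot be evaluated at weeks 2, 4 or 6 either. Repeating the categorical analysis there needs a single-visit definition, which the article does not give.

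**Step 2: apply the rule to each possible pattern.**

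| Week 8 score 0 or 1 | Week 12 score 0 or 1 | Time in relief within the window | Result |
|---|---|---|---|
| yes | yes | 4 weeks, if relief is assumed continuous | relief, by assumption |
| no | no | 0 weeks, if non-relief is assumed continuous | no relief, by assumption |
| yes | no | unknown, anywhere between 0 and 4 weeks | undetermined |
| no | yes | unknown, anywhere between 0 and 4 weeks | undetermined |
| either score missing | | unknown | undetermined |

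For a discordant patient the two-week threshold lies in the middle of the possible range, so the data do not favour either answer.

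**Step 3: how many patients could this affect?** For missing scores, the plan's 20% dropout is 0.20 × 20 = 4 per arm. Those who leave after at least one evaluable follow-up stay in the intent-to-treat set as defined, but may have no week 12 score.

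For discordant scores the documents give no figures, so the following is an illustration under assumptions. Let p be the probability of a qualifying score, the same at weeks 8 and 12, let r be the within-patient correlation, and let no score be missing.

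- Discordant share = 2p(1 − p)(1 − r)
- Rate if both scores must qualify = p² + r·p(1 − p)
- Rate if either is enough = 2p − (rate for both)

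| p | r | Discordant | Of 20 per arm | Both | Either |
|---|---|---|---|---|---|
| 0.3 | 0.3 | 29.4% | 5.9 | 15.3% | 44.7% |
| 0.3 | 0.5 | 21.0% | 4.2 | 19.5% | 40.5% |
| 0.3 | 0.7 | 12.6% | 2.5 | 23.7% | 36.3% |
| 0.5 | 0.3 | 35.0% | 7.0 | 32.5% | 67.5% |
| 0.5 | 0.5 | 25.0% | 5.0 | 37.5% | 62.5% |
| 0.5 | 0.7 | 15.0% | 3.0 | 42.5% | 57.5% |
| 0.6 | 0.3 | 33.6% | 6.7 | 43.2% | 76.8% |
| 0.6 | 0.5 | 24.0% | 4.8 | 48.0% | 72.0% |
| 0.6 | 0.7 | 14.4% | 2.9 | 52.8% | 67.2% |

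Worked line for p = 0.5, r = 0.5: both = 0.25 + 0.5 × 0.25 = 0.375; either = 1 − 0.375 = 0.625; the gap of 0.25 is the discordant share.

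**The case against.** The best defence is that this is a condensed article, that the full protocol might hold a symptom diary, and that a sensible analyst would read the rule as qualifying at both week 8 and week 12. The diary argument fails because the article itself states the total number of relief responses and when they are given. The second argument has some force: most patients may be concordant, and for them the reading is natural. It is still unstated, and it does not settle missing scores or the analyses at other weeks.

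Other parts of the defence stand and limit the point:

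- A reader might infer that the primary outcome is undefined or that hypothesis 2 goes untested. The documents do not support this. The 0 to 4 score is analysed separately by ANOVA and Kruskal-Wallis, and analyses at week 8 are planned.
- A reader might infer that the window is wholly off treatment and so aimed at the wrong period. Week 8 is the end-of-treatment visit, and persistence of relief is a legitimate question: the Introduction cites a lasting effect of otilonium bromide.
- A reader might infer from "by dividing the number of participants who exhibited sufficient symptom relief by the total number of participants in the trial" that each arm's rate is to be divided by all 80 patients. The phrase concerns a descriptive rate and may mean one overall rate. The χ² or Fisher's exact comparison works on counts within arms, so inference is unaffected.
- A reader might infer that the scale direction contradicts itself, because "the improvement is given a score of 0, 1, 2, 3 or 4" could suggest that higher is better. That section states no direction, the Statistical analysis section supplies one, and response anchors are commonly left to the full protocol.

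**Conclusion.** The point holds as a contradiction between the relief rule and the assessment schedule, both stated in the article. The rule cannot classify patients with discordant or missing week 8 and week 12 scores, and it classifies the others only under an unstated assumption of continuity. It has no meaning at weeks 2, 4 and 6, and the week-10 analysis has no data from any of the 80 patients.

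The schedule findings need no assumption. The size of the unclassifiable group does: the range of about 13% to 35% rests on the assumed rates and correlations, not on figures in the document. The consequence is confined to the relief rate and the categorical analyses built on it. The analysis of the score itself is unaffected.

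**What to change.** Before unblinding, amend the Statistical analysis section as follows.

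- Define response on collected scores. For example, use a score of 0 or 1 at week 8 for the end-of-treatment effect in hypothesis 2, and a score of 0 or 1 at both weeks 8 and 12 as a separate sustained-relief outcome.
- State how a missing week 8 or week 12 score is handled in each definition.
- For the repeat analyses, use the single-visit definition and replace week 10 with week 12.
- Word the descriptive rate as responders divided by the analysed patients in that arm, so that it matches the stated intent-to-treat and per-protocol sets.

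This is a wording change and needs no new visits or data. The small downside is that sustained relief is then reported separately from the end-of-treatment response.
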